### Procedure

2.3

Posters and online announcements of the study will be created and sent to the five universities mentioned above. The project website, advertising posters, academic institutions' websites, and social media sites will all be used to announce the study. Students will be able to navigate to the project website by scanning the QR code on the posters.

Upon accessing the project website, participants will be asked to complete an online informed consent form outlining the study's aims before deciding whether to volunteer. After obtaining the participants' consent to volunteer in the study, they will be requested to fill out the questionnaires. Those who meet the remaining inclusion requirements but score highly on PHQ-9 and GAD-7 or undergoing psychological treatment will not be able to register or access the system. These users will be notified to seek professional help if they so choose, along with a window with contact details for resources (counseling center of the university, medico-social units) that will enable them to receive help at the appropriate university. Allotted participants will get e-mails and SMSs letting them know which group they are in. To guarantee the validity and reliability of our results, we want to take this heterogeneity into consideration during our analysis procedures. The consort flow chart of the study is presented in Fig. 1.

In the qualitative part, to ensure diversity in the semi-structured interview process, participants who discontinued the program with the lowest and highest symptom levels will be invited, while maintaining a balanced gender ratio. This stratified approach aims to capture a wide range of perspectives. The interviews will be conducted by researchers holding doctoral degrees in psychology, ensuring both expertise and consistency in data collection.

### Randomization

2.4

Through the use of software (randomizer.org), participants who have registered on the project website and fulfilled the inclusion criteria will be assigned to groups randomly. Care will be given to guarantee that the distribution of men and women is equal to achieve maximum variety in each group. Therefore, the randomizer.org website's block approach will be utilized. Participants will remain blinded to their group assignment to minimize bias. Group assignment will be managed by a third party using coded identifiers. Participants in the intervention group will immediately access the program, while those in the waitlist control group will be informed that the program will not start immediately for them but will be made available after a waiting period. Both groups will receive equivalent instructions and communication to ensure they cannot discern their allocation. This approach balances expectations and perceived fairness, reducing potential bias in participant responses.

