## Abstract

University students often face significant mental health challenges, including depression, anxiety, and difficulties in adjustment, which can be exaggerated by the demands of independent living and increased life responsibilities. These challenges are often compounded by barriers to seeking help, such as stigma and limited access to university resources, which can further deteriorate students' well-being. This protocol was created to assist college students in overcoming these obstacles and to assess, in comparison to a control group, the impact of a guided and unguided online intervention platform based on transdiagnostic CBT (UNIPDES) on depression, anxiety, and adjustment levels. The calculated sample size for the study will include 330 students, and the participants will be selected from five different universities located in Türkiye. Participants will be randomly assigned to either guided, unguided, or control groups. Guided and unguided group participants will receive six weeks of intervention, and the waitlist control group will receive the unguided version of the program after twelve weeks of randomization. Assessments will take place at baseline, post-test (8 weeks post-baseline) and follow-up (12 weeks post-baseline). A Mixed ANOVA will be employed to analyze the data, with Group (Guided, Unguided, Control) as the between-subjects factor and Time (Baseline, Post-Test, Follow-Up) as the within-subjects factor, as well as to assess the interaction effect between Group and Time on the primary outcomes—changes in depression, anxiety, and adjustment levels. Additionally, students’ reasons for dropout will be assessed qualitatively. The results from this study can build evidence for the effectiveness of transdiagnostic guided and unguided internet-based intervention for treating depression, anxiety, and adjustment problems of students. UNIPDES can provide a flexible, easy-to-access, and cost-effective treatment for the problems that students commonly face. Trial registration is registered at ClinicalTrials.gov Protocol Registration and Results System (Trial number: NCT06245200).

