### Sample size estimation

2.5

The G∗Power program [65] was utilized to determine the sample size. The program's objectives included three groups, three assessments, four covariates (depression, anxiety, adjustment, and attitude toward internet-based interventions score), a medium effect size (Cohen's *d* = 4, Cohen's *f* = 2), a power of 80 %, and a significance level of *p* = 0.05. Therefore, a minimum sample size of 244 individuals is needed to detect a significant difference.

It is important to consider dropout rates while determining the sample size. Based on their review from the studies between 1990 and 2009, Melville et al. [37] found that the dropout rates range from 2 to 83 %, with an average rate of 31 % in internet-based interventions. Another meta-analysis by Meyerowitz-Katz and colleagues [38] reported the average attrition rate in internet-based interventions as 43 % in studies published in between 2011 and 2019. Based on the previous research (also see Ref. [66,67]), a 35 % dropout rate is anticipated for this study. The dropout rates for internet-based interventions are comparable to those in previous studies based on traditional counseling interventions [68], in their meta-analysis, reported that 55 % of total participants completed the internet-based treatments.

In light of the power analysis calculated through G∗power software, it is suggested that each group should contain 81 people. Due to our expectation of a 35 % dropout rate, an additional 30 participants will be added to each group.

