### Statistical analyses

2.10

A Mixed ANOVA will be employed to analyze the data, with Group (Guided, Unguided, Control) as the between-subjects factor and Time (Baseline, Post-Test, Follow-Up) as the within-subjects factor. This approach will assess both the main effects of Group and Time, as well as the interaction effect between Group and Time on the primary outcomes—changes in depression, anxiety, and adjustment levels. Post-hoc tests will be conducted to explore significant interactions. If necessary, covariates will be included in the analysis through a Mixed ANCOVA to adjust for baseline differences.

Dropout and missing data are anticipated in the study. To address this, missing data will be handled using relevant methods, e.g., multiple imputation or Multilevel Mixed-Model Regression Analysis, depending on the nature and pattern of missingness. Multiple imputation will be employed to estimate missing values if the data are missing at random, while Multilevel Mixed-Model Regression Analysis will be applied to account for both missing data and repeated measures over time. Baseline characteristics across the three groups will be tested using statistical methods such as t-tests, chi-square tests, or ANOVA to ensure comparability. Any significant differences will be adjusted for in subsequent analyses. These approaches will help ensure the robustness of the findings despite anticipated dropout and missing data.

The qualitative data will be transcribed and coded into themes by two independent researchers to ensure reliability. In the analysis of the data, the MAXQDA program will be utilized. According to the principles of [81] to ensure the reliability and validity of the results, the coding and assignment of themes will be conducted by several researchers, and the evaluation will be made through consensus/(disagreement + agreement) ∗100 formula as suggested. At the end of the analysis, consensus and disagreements will be evaluated in a project team meeting.

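### The block approach named in section 2.4 does not by itself balance gender across arms, and if blocks are formed within gender, the analysis leaves that factor out

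*Protocol article*

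**What the plan says.** Section 2.4 (Randomization) of the protocol article sets the aim: "Care will be given to guarantee that the distribution of men and women is equal". The next sentence names the means: "Therefore, the randomizer.org website's block approach will be utilized". The section mentions no strata and no separate lists for men and women. The only stratified approach in the article (section 2.3) concerns the choice of interviewees.

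The Abstract describes three arms ("Participants will be randomly assigned to either guided, unguided, or control groups") and 330 students. Section 2.5 gives 81 + 30 = 111 per group.

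Section 2.10 fits a mixed ANOVA with Group and Time as its only factors, and adds: "If necessary, covariates will be included in the analysis through a Mixed ANCOVA to adjust for baseline differences". It also says that baseline characteristics will be tested and significant differences adjusted for. The covariates named in sections 1.2 and 2.5 are the baseline depression, anxiety, adjustment and attitude scores. Gender is recorded on the demographic form (section 2.9.2.1) but appears in no named model or covariate list.

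**The concern.** The article presents gender balance as following from blocking. A permuted block fixes how many of the next few students go to each arm, whatever their gender, so the promised property does not follow from the named method. Gender is the one characteristic the sponsor singled out for balance, and an allocation cannot be repaired once enrolment is over.

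The other reading is that blocks will be formed within gender. The promise is then broadly met, but gender becomes part of the randomisation scheme and would ordinarily be in the model. Here it could enter only through a significant baseline test, and a factor balanced by design will hardly ever produce one. Each reading therefore leaves something to put right, in the allocation or in the analysis.

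**Working it through.** **Inputs.** From the article: three arms; 111 per arm (section 2.5); f, printed as 2 and read as 0.2; four covariates; minimum N of 244. Not given, so assumed: 50 to 70% women among those enrolled (80% where stated), blocks of 6, and gender explaining 1 to 10% of the residual outcome variance.

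**The plan's own figure.** For an ANCOVA F-test with f = 0.2, df1 = 2, df2 = N - 3 - 4 and noncentrality f² x N, N = 244 gives 0.04 x 244 = 9.76 and power 0.8001. The stated 244 is reproduced. The point about gender balance does not depend on it.

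**Reading 1: blocks not formed within gender.** Allocation ignores gender, so the number of women in each arm is binomial (111, p). One arm's share of women has SD √(p(1-p)/111), which is 4.75 points at p = 0.5 and 4.35 at p = 0.7. The expected range of three such values is about 1.69 SD, or 8.0 and 7.4 points. A gap of at least 10 points means 12 students or more, since 0.10 x 111 = 11.1. Simulation with 200,000 draws:

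| Women enrolled | Chance of a gap of 10 points or more | Of these, flagged by a chi-square test at 0.05 |
|---|---|---|
| 50% | 27% | 18% |
| 60% | 26% | 20% |
| 70% | 21% | 24% |

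The threshold is lumpy. With 110 per arm (330/3), 11 students is exactly 10 points, and counting that case gives 33, 32 and 27%. The last column shows that the significance rule in section 2.10 would pass over most such gaps.

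**Reading 2: blocks within gender.** With N = 330, blocks of 6 and 50 to 80% women (20,000 runs per setting), the mean gap is 0.6 to 0.7 points, the 95th percentile is 1.4 to 1.6 points, and no run reached 10 points. A baseline test of gender would then practically never be significant.

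**Cost of omitting gender under reading 2: between-group test.** If gender explains a fraction R² of the residual variance and is balanced, the true size is P(F > 3.024/(1 - R²)) on 2 and 323 df (323 = 330 - 3 - 4). Power at N = 244 uses noncentrality 9.76/(1 - R²):

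| R² | Size | Power, gender omitted | Power, gender included |
|---|---|---|---|
| 0.01 | 0.0485 | 0.801 | 0.804 |
| 0.03 | 0.046 | 0.802 | 0.813 |
| 0.05 | 0.043 | 0.803 | 0.821 |
| 0.10 | 0.036 | 0.807 | 0.843 |

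The loss is about 0.4 to 3.5 points of power.

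**Cost of omitting gender under reading 2: Group x Time.** This is tested against within-person error, where a gender effect that is constant over time cancels. In a simulation with three gender-balanced arms of 80, gender omitted and constant gender effects of 0, 0.5 and 1 SD, the size of the interaction test was 0.051, 0.048 and 0.050. The Group main effect went to 0.049, 0.039 and 0.017. The interaction is affected only if gender predicts change. For a gender difference of δ SD in change scores and an even split, R² = (δ²/4)/(1 + δ²/4), and the two-sided size of a pairwise comparison is 2(1 - Φ(1.96/√(1 - R²))). That is 0.049 at δ = 0.2 and 0.041 at δ = 0.6.

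**The case against.** The best defence is that section 2.4 states a gender aim and then a block method, so that blocking by gender is the natural, if loosely worded, reading. Strata, block sizes and list generation are details that an article may leave to the full protocol, and the final covariate list to an analysis plan. This stands in part: if the full protocol already specifies separate lists, the allocation half becomes a matter of wording. It does not settle the analysis half. The article itself fixes the model factors and names the covariates, and its only other route into the model is a test that blocks within gender would render idle.

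It is also fair to object that the consequences are small. A 10-point gap multiplied by an assumed gender difference of 0.2 to 0.5 SD moves an arm contrast by 0.02 to 0.05 SD, and chance imbalance of this kind is already allowed for in the test's significance level. This stands in full and sets the weight of the point.

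Three stronger readings are not supported:

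- A reader might infer from the promise of care that allocations will be corrected by hand and so become predictable. No section describes this. Section 2.4 names software and has a third party manage assignment with coded identifiers.
- A reader might infer that omitting gender widens the standard error of every comparison. For Group x Time it does so only where gender predicts change.
- A reader might recompute the gender gap among those remaining after the anticipated 35% dropout. That mixes attrition with allocation. Section 2.9 also assesses everyone at week 8, whether or not they completed the program.

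**Conclusion.** The point holds and is minor. As written, the method in section 2.4 does not deliver the gender balance it promises: with unstratified blocks and 111 per arm, a gap of 10 points or more in the share of women arises in about 21 to 27% of trials. Even blocks within gender equalise the ratio across arms, not the numbers of men and women inside an arm, so the guarantee is too strong on either reading.

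If blocks are within gender, the planned analysis ignores a randomisation factor. The Group main effect is then mildly conservative (size 0.036 to 0.0485, with 0.4 to 3.5 points of power lost). Group x Time is touched only to the extent that gender predicts change. Randomisation stays valid on both readings, with no bias and no inflated type I error. The figures rest on the assumed share of women, block size and variance explained by gender, none of which the article gives.

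**What to change.** In section 2.4, state that the third party generates two block lists before enrolment, one for men and one for women, with block sizes not disclosed to those who enrol. Replace the guarantee of equality with similar gender ratios across arms.

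In section 2.10, prespecify gender and gender x time as terms in the primary model for each outcome, whatever the baseline tests show. The main effect alone would help only the Group comparison; the gender x time term is what serves Group x Time.

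The cost is one extra list and, with three assessments, 1 + 2 = 3 degrees of freedom. Gender is already collected at baseline, so no new data are needed.

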### Guidance

2.7

After random assignment of participants into three groups (guided, unguided, or control), participants in the guided group will receive expert-written feedback within 24 h of each module's completion. Feedback will be delivered by researchers (guides) working on the project as scholars and these researchers/guides will receive two days of training from two specialists who are experts in CBT and TA. The researchers (guides) working on this project have been educated in psychology/counseling fields (at least a master's degree) and have previous experience in the CBT approach. All the feedback provided by guides to program users will not exceed 300 words. The feedback will not include therapeutic intervention beyond what is offered in the program, as the feedback's main goal is to encourage/motivate the participant. The other/next module will start after the feedback message has been sent. Before sending feedback to participants in the guided group, all the feedback composed by researchers/guides will be checked and approved by those who train guides to maintain consistency across researchers/guides.

Participants in the unguided group will utilize the program entirely on their own and will not receive regular feedback upon module completion. The next module will be available the day after the previous one is finished. Participants in both guided and unguided groups will receive reminder messages on the third and fifth days if they have not yet begun the next module in the program.

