### Control condition

2.8

The waitlist control (WLC) group will be asked to complete pre- and post-assessments at initial registration and by the end of the eighth week. Participants will not be in contact with the research team throughout the waiting period. They will be given the unguided version of the program at the 12th week, after the completion of the assessment tools. Participants who complete all measurement tools will receive a gift card (which they can spend on numerous web pages) as a means of encouragement.

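### Section 2.4 says participants are blinded to their group, but section 2.3 tells them their group and section 2.4 itself tells the waitlist that its program is delayed

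*Protocol article*

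**What the plan says.** Section 2.4 (Randomization) makes three linked statements. The first is the claim itself: "Participants will remain blinded to their group assignment to minimize bias". The second gives the means: "Both groups will receive equivalent instructions and communication to ensure they cannot discern their allocation". The third gives the benefit: "This approach balances expectations and perceived fairness, reducing potential bias in participant responses".

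Section 2.3 (Procedure) describes what happens after allocation: "Allotted participants will get e-mails and SMSs letting them know which group they are in".

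Between its claims, section 2.4 also says that the intervention group gets access at once, while "those in the waitlist control group will be informed that the program will not start immediately for them".

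The arms then differ in what participants experience. In section 2.7 (Guidance), "participants in the guided group will receive expert-written feedback within" 24 hours of finishing each module, whereas "Participants in the unguided group will utilize the program entirely on their own and will not receive regular feedback upon module completion". Both active arms get reminders if they have not begun the next module. Section 2.8 (Control condition) says of the waitlist arm: "Participants will not be in contact with the research team throughout the waiting period".

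**The concern.** Sections 2.3 and 2.4 are both current text about the same people and the same fact, and they cannot both be true. Participants either know their group or do not.

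It matters because of who supplies the outcome data. Section 2.10 names changes in depression, anxiety and adjustment as the primary outcomes, and the instruments are questionnaires that participants fill out. When respondents know their arm, expectation in the active arms and disappointment in the waitlist arm can shift answers without any change in the underlying state. Blinding is the device section 2.4 relies on to limit this. If it is absent, the stated protection is absent too, and a results paper that repeated the sentence would misinform anyone rating risk of bias.

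**Working it through.** No arithmetic applies: the protocol gives no figure for reporting bias and none can be derived from it. The check sets the sections side by side.

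1. **Claim against disclosure.** Section 2.4 says participants stay blinded to group. Section 2.3 says those allotted are told their group by e-mail and SMS. In context, those allotted are the people randomised. This step alone defeats the claim for all three arms, provided the message does what section 2.3 says it does.

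2. **Section 2.4 against itself.** One group gets the program at once and the other is told it must wait. A participant told to wait knows that he or she is in the waitlist arm, and one given immediate access knows that he or she is not. So even without section 2.3, active versus waitlist cannot be concealed.

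3. **Guided against unguided.** The guided arm gets written feedback after each module and the unguided arm does not. On its own this need not reveal allocation, because a participant who does not know that another format exists has nothing to compare with. What defeats masking here is the message in section 2.3.

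4. **Equivalent communication.** Section 2.4 speaks of two groups in a three-arm trial. The natural reading is intervention versus waitlist. Feedback and reminders go to active participants, while the waitlist arm has no contact with the research team during the wait. This sits badly with equivalence. It is secondary evidence, because the phrase could refer only to messages at enrolment and allocation.

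5. **Does another provision rescue the claim?** Section 2.4 has a third party manage assignment with coded identifiers. That could support concealment of allocation or masking of staff. It does not keep from participants what they are told directly. Reading the claim as blinding only up to assignment also fails, because the sentence says that blinding continues and the later one says that allocation cannot be discerned.

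6. **Which data are exposed.** Under section 2.3, questionnaires are completed at registration, before allocation is announced, so the baseline scores precede knowledge of the arm. Section 2.9 places T1 at 8 weeks and T2 at 12 weeks. Section 2.8 gives the waitlist the program at week 12, after the assessment tools are completed. Both post-baseline assessments are therefore answered while waitlist participants know that they are waiting. Knowledge of the arm is absent at baseline and present at T1 and T2, so any reporting shift it causes enters the Group by Time interaction that section 2.10 plans to test. This applies to 3 of 3 primary outcomes.

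**The case against.** The best case on the other side has four parts.

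- **This is ordinary for the design.** Participants in a waitlist trial usually know that they are waiting. That is right, and an open-label waitlist comparison is a legitimate choice. The error is in describing it as blinded.

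- **The limitation is already conceded.** The Discussion (section 3) names the waitlist control as a drawback and says that treatment effects may be overestimated. This stands in part: a reader might infer that the authors overlooked the problem, and they did not overlook it entirely. But that text points to external factors and to minor improvement among controls. It does not mention unblinded self-report and does not withdraw the blinding claim.

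- **Masking of guided versus unguided is feasible.** This stands. A reader might infer that blinding is impossible throughout, and the document does not support that. Between the two active formats it fails because of the allocation message, whose exact wording is not shown.

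- **The protocol's claim is modest.** A reader might take section 2.4 to say that bias has been eliminated. It speaks only of minimising and reducing bias. The weaker claim still rests on blinding that the protocol does not deliver.

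**Conclusion.** The protocol states a design property that it does not have. Participant blinding is contradicted by section 2.3 for all arms, and by section 2.4 itself for active versus waitlist. All three primary outcomes, at both post-baseline assessments, are reported by people who know their arm.

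On size and direction, the document supports only a limited conclusion. Overestimation is likely mainly in the guided-versus-waitlist and unguided-versus-waitlist contrasts, which agrees with the concern the Discussion already raises. Its size cannot be derived. It is tempting to say that every comparison is biased in a known direction, but both guided and unguided participants receive the program and nothing in the text fixes a direction between them. Nor does the finding invalidate the design, the planned model or the sample size. It changes what may be claimed about bias.

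Two assumptions are used. The first is that the allocation message names the group as section 2.3 says. The second is that the questionnaires at weeks 8 and 12 are completed by participants themselves, as at entry; section 2.8 also describes the waitlist group completing its own assessments.

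**What to change.** Reconcile sections 2.3 and 2.4 in one of two ways.

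- **Preferred:** remove from section 2.4 the sentence claiming blinding, the sentence claiming that allocation cannot be discerned, and the bias-reduction claim that rests on them. State that the trial is open-label for participants and that the primary outcomes are self-reported. The account of the third party and the coded identifiers can stay, with its purpose stated.

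- **Alternative:** if something is in fact withheld, such as the hypotheses or the existence of the other program format, say exactly what it is and align the allocation message in section 2.3 with it. Describe this as partial masking. It cannot cover active versus waitlist.

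Under either option, extend the waitlist limitation in the Discussion to name unblinded self-report as a source of overestimation, and qualify conclusions from the two waitlist contrasts accordingly. Keeping the analyst masked to arm labels would be a reasonable addition, but it is optional and does not repair the contradiction.

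The preferred option costs wording only. The alternative may also require a changed participant message and a check against the information booklet and consent form, which section 2.1 says the ethics committee has approved. Neither option alters the sample size, the allocation procedure or the analysis model.
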